### Participant timeline {13}

The time schedule of enrolment, interventions, follow-up, and assessments in the main trial is summarised in a SPIRIT figure (Fig. 2). In addition, long-term registry data withdrawal is planned.

**Fig. 2 Fig2:**
[figure not shown]
Schedule of enrolment, interventions, and assessments. Abbreviations: BNSQ = Basic Nordic Sleep Questionnaire, CAT = Chronic Obstructive Pulmonary Disease Assessment Test, DES = Dyspnea Exertion Scale, eCRF = electronic Case Report File, EQ 5D 5L = EuroQol 5 Dimension 5 Levels, HFOT = High-Flow Oxygen Therapy, LFOT = Low-Flow Oxygen Therapy

### Sample size {14}

The sample size will be 270 randomised people with COPD and with data on the primary outcome. This sample size was determined to provide 80% power to detect a clinically meaningful between-group difference in the primary outcome (time to first hospitalisation or death from all causes during 1 year) of hazard ratio 0.67 in people with COPD, using a two-sided test, assuming equal allocation between the treatment groups, a 1-year rate of the primary outcome of 0.74 in the target population in the Swedevox registry; and a false positive rate (alpha) of 0.05 [33].

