### Interim analyses {21b}

No interim analyses will be performed, but the final number of randomised people needed to reach the target sample size will be checked before closure of trial enrolment, to ensure adequate power in the analysis of the primary outcome.

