## Discussion

This is the largest multi-centre RCT to assess the benefits of HFOT to date, and the first to include people with ILD. The study will have power to assess mortality and hospitalisation as a primary outcome and health-economics as a secondary outcome. Although LFOT is an established treatment that improves survival in people with chronic respiratory failure and severe hypoxemia [1, 2], the risk of hospitalisation and death in people with LFOT is very high [5, 8], and it is of great importance to assess interventions that may improve the prognosis. In addition, people with LFOT experience a high burden of local side effects with an impact on their HRQL [6], and HFOT could potentially decrease these problems.

The trial started with a pilot phase at the centres in Örebro and Karlskrona, to evaluate feasibility and therapy adherence. Early challenges were identified, particularly related to patient adherence due to device-related discomfort, as the majority of people randomised to HFOT were non-adherent and chose to end the treatment. The most common reasons were difficulties in sleeping due to discomfort and noise from the device. As a consequence, adjustments in initial flow settings and patient education strategies were made. The standard procedure was changed to aim for an initial lower oxygen flow of 20 L/min to get used to the high oxygen flow and to preferably use a somewhat larger nasal cannula to reduce the sound from the gas flow. In addition, a notification that it may take a couple of weeks to adjust to the new treatment was added to the standard information at the baseline visit.

Until end of spring 2025, start meetings have been held at the remaining sites, and the study is now recruiting at all ten sites.

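### The 270 people and 80% power follow only if 0.74 is the event rate averaged over both arms; as the usual-care rate it describes, 0.74 gives about 180 events and about 77% power

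*Protocol article*

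**What the plan says.** The section Sample size {14} fixes the target: "The sample size will be 270 randomised people with COPD and with data on the primary outcome". It continues: "This sample size was determined to provide 80% power to detect a clinically meaningful between-group difference in the primary outcome", with an effect "of hazard ratio 0.67 in people with COPD", "using a two-sided test, assuming equal allocation between the treatment groups", alpha 0.05, and "a 1-year rate of the primary outcome of 0.74 in the target population in the Swedevox registry". It gives no separate rate for the HFOT arm and no expected number of events.

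Three other sections show whom the 0.74 describes. Study setting {9} says the people screened are registered in Swedevox because of ongoing LFOT. Eligibility criteria {10} exclude current or previous home HFOT. The section on the choice of comparators {6b} defines the control arm as continued LFOT under usual care.

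Interim analyses {21b} plans no interim analysis but says that "the final number of randomised people needed to reach the target sample size will be checked before closure of trial enrolment", with the aim of securing power for the primary outcome.

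**The concern.** A rate observed in people on usual care is the rate to expect in the control arm. If HFOT lowers the hazard by a third, the HFOT arm must have a lower 1-year rate, and the two arms together must fall below 0.74. Power for a log-rank or Cox comparison depends on the total number of events, so applying 0.74 to all 270 people overstates the information the trial will have.

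Two things are at stake. A null result would be read against a power that the stated inputs do not give. And the one check planned before enrolment closes counts people, so it would be passed at 270 whatever the number of events.

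**Working it through.** **Inputs**, all from Sample size {14}: N = 270 (135 per arm), hazard ratio (HR) 0.67, two-sided alpha 0.05, power 80%, equal allocation, 1-year rate 0.74. Follow-up for the primary outcome is 1 year (Outcomes {12}). The check assumes proportional hazards and complete 1-year follow-up, since the 270 are to have outcome data.

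**1. Events needed.** Schoenfeld: 4 × (1.960 + 0.842)² / (ln 0.67)² = 195.8, so 196. Freedman: (1.960 + 0.842)² × (1.67/0.33)² is just over 201, so 202.

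**2. The plan's own figure, with 0.74 as the average over both arms.**
- N = 196/0.74 = 265 (Schoenfeld) or 202/0.74 = 273 (Freedman). Both are close to 270.
- Events at N = 270: 270 × 0.74 = 199.8.
- Power (Schoenfeld): Φ(0.4005 × √199.8 / 2 − 1.960) = 80.8%. Freedman gives 79.8%.

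So the plan's figure is reproduced. For 0.74 to be the average at HR 0.67, the arms must have rates p and 1 − (1 − p)^0.67 with mean 0.74. This gives p = 0.81 in the control arm and 0.67 in the HFOT arm. The article does not state a control rate of 0.81.

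**3. The same inputs with 0.74 as the control rate.**
- HFOT rate: 1 − (1 − 0.74)^0.67 = 1 − 0.26^0.67 = 0.594.
- Average: (0.74 + 0.594)/2 = 0.667.
- Events: 270 × 0.6672 = 180, about 16 fewer than the 196 needed.
- Power (Schoenfeld): Φ(0.4005 × √180.2 / 2 − 1.960) = 76.7%. Freedman gives 75.6%. A log-rank simulation with 20,000 trials gives 76.5%.
- N that would give 80%: 195.8/0.6672, so 294 (Schoenfeld), or 303 (Freedman).

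**4. The gap expressed as an effect size.** At HR 0.66 the HFOT rate is 1 − 0.26^0.66 = 0.589, the average 0.664 and the events 179.4. Power is Φ(0.4155 × √179.4 / 2 − 1.960) = 79.5%.

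**5. Other readings of 0.74.** As a hazard of 0.74 per year, the 1-year risks are 0.523 and 0.391, giving 123 events and 60% power. A comparison of two proportions, 0.74 against 0.594, needs 164 per arm. Neither gives 270.

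**The case against.** **Pooling is an inference.** The article never says that 0.74 is an average over both arms, and the cited method source is not at hand. That is true. But of the readings tried, only this one reproduces 270, and the shortfall does not depend on it: it follows from 0.74 being a usual-care rate.

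**The planned analysis is adjusted.** Statistical methods {20a} specifies a Cox model with age, sex, the stratification variables, prior hospitalisations and time since LFOT start, whereas 77% is unadjusted power. A simulation of the adjusted model assumed a standard deviation of 0.4 or 0.6 for the covariates' combined log-hazard effect. It gave about 80% or 87% power if 0.67 is a marginal hazard ratio, and about 76% or 78% if it is conditional on the covariates. So adjustment might close the gap. But the prognostic strength is assumed, and the sample-size section mentions neither adjustment nor a marginal hazard ratio. The stated justification does not rest on this.

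**A registry rate is only approximate, and 3 points is small.** This stands, and it limits the weight of the point.

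**Stronger readings that the documents do not support.**
- *Non-adherence.* The Discussion reports that in the pilot "the majority of people randomised to HFOT were non-adherent and chose to end the treatment", and a reader might infer that the trial is badly underpowered. If 0.67 were the effect in people who stay on treatment, and the log hazard ratio shrank in proportion to the share without benefit, power would be about 58% with 20% and 28% with 50% of the HFOT arm without benefit. The article gives no stopping rate, and it reports changes to the starting procedure, cannula and patient information made in response. It also presents 0.67 as the between-group difference, in a trial analysed primarily by intention to treat. The natural reading is that 0.67 is already the intention-to-treat target.
- *Mortality alone.* The Discussion says "The study will have power to assess mortality and hospitalisation as a primary outcome and health-economics as a secondary outcome". A reader might take this as a claim of power for mortality on its own. Since the primary outcome is hospitalisation or death, it reads most naturally as the composite.

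**Conclusion.** The power statement is wrong as written, and the error is modest. From the plan's own inputs, with 0.74 in the arm it describes, 270 people give about 180 events and about 77% unadjusted power for HR 0.67, not 80%. The shortfall is about 3 percentage points, or 24 to 33 people at 80% power, depending on the formula. It rests on proportional hazards, on complete 1-year outcome data, and on the registry rate applying to the trial's control arm.

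The check before enrolment closes does not correct this, because its target is a head count. It remains useful for its stated purpose of reaching 270 people with outcome data. The point does not show that the trial is seriously underpowered, nor that its size must change.

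**What to change.** 1. In Sample size {14}, restate the justification: control rate 0.74, HFOT rate about 0.59, about 180 expected events, and about 77% power for HR 0.67 (79.5% at HR 0.66). If 0.74 was meant as an average over both arms, say so and give the basis for a control rate of about 0.81.
2. In the same section, say that 0.67 is the intention-to-treat effect the trial targets. Power at one or two assumed adherence levels may be added. It should be marked as illustrative, because no stopping rate is given and the procedures changed after the pilot.
3. In Interim analyses {21b}, note that a head count of 270 does not by itself ensure 80% power, because power depends on events. I would not add a fixed threshold of 196 events: about 180 are expected from 270 people, and those enrolled last will not have completed 1 year when enrolment closes.

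The cost is wording. The stated power becomes slightly less favourable, and no more patients are required.

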### Recruitment {15}

People with ongoing LFOT in the Swedevox registry are identified and screened for enrolment at the participating centres. In accordance with Swedish legislation and regulations, people starting LFOT are given written information about Swedevox including the choice to opt out from registration in Swedevox or for their data to be removed from the register at any time. People who do not opt out are registered in Swedevox, which has a high and stable nationwide coverage of about 85% of people starting LFOT in Sweden [5]. All people at participating units who are using LFOT since at least 28 days in the Swedevox registry will be screened for participation in the study.

## Assignment of interventions: allocation

### Sequence generation {16a}

Randomisation is performed within the web-system REDCap, a combined electronic Case Report File (eCRF) and randomisation module. The allocation is generated in blocks between 2 and 8, to reduce predictability of the sequence to the investigator.

### Concealment mechanism {16b}

The randomisation is computerised within the web-system REDCap, which means that the allocation is fully concealed until randomisation is performed.

### Implementation {16c}

The allocation sequence is generated by the web-system REDCap, and the local PI will enroll people and assign them to intervention according to randomization. 

## Assignment of interventions: blinding

### Who will be blinded {17a}

Due to the nature of the intervention (distinctive HFOT device setup), blinding of people and clinical staff is not feasible. However, the statistical analyst will remain blinded to allocation until database lock to minimise bias.

### Procedure for unblinding if needed {17b}

Non-applicable.

## Data collection and management

### Plans for assessment and collection of outcomes {18a}

Outcome data will be obtained from patient questionnaires at baseline, 3 and 12 months, from Swedevox, from trial specific data entered in the eCRF by the PIs, and from national registries. In centres using the remote home-monitoring system AirView, data on HFOT utilisation will be used.

The questionnaires will include questions on oxygen and HFOT usage, patient preference for continuing the treatment, utilisation of primary care and domestic service, adverse events, and the number of exacerbations since the start of the trial. Symptoms included in the questionnaires are breathlessness using a modified Dyspnoea Exertion Scale (DES) [34] and the Dyspnoea-12 questionnaire [35, 36], cough and phlegm assessed by relevant items in the COPD Assessment Test (CAT) [37], sleep complaints using a modified Basic Nordic Sleep Questionnaire (BNSQ) [38], nasal symptoms, and subjective perception of change in health status assessed with a modified Global Impression of Change (GIC) scale [39]. Physical activity is reported for the previous month using a modified Grimby activity questionnaire [40, 41], and HRQL is evaluated using the CAT [37] and EuroQol Five Dimensions Five Levels (EQ5D-5D-5L) [42].

Data from Swedevox will be used for characterising the people and their oxygen treatment, and for assessment of rate and reason of LFOT withdrawal during follow-up. The ventilator arm of the Swedevox registry will be used to assess the incidence of long-term home mechanical ventilator usage.

If applicable, data on HFOT utilisation will be collected from centres using Airview at 1 week, 3 and 12 months on: average usage time, daytime and nighttime use, days of use, and days of use ≥ 4 h/24 h. Data on oxygen flow and HFOT settings will be collected from staff-reported questionnaires at 3 and 12 months.

Data from the National Patient Registry from 1 January 1997 to end of trial for all in and outpatient care will be used to assess comorbidities at baseline, and time to, rate, and reason of hospitalisation and incident conditions and procedures during follow-up. Data from the Drug Registry on all dispensed outpatient prescriptions will be obtained from 1 year before the date of randomisation until the end of follow-up in the study. Data from the Intensive Care Registry on length of stay, procedures, treatments, complications, and death will be obtained to assess ICU care from 365 days before randomisation throughout follow-up. Data from the Cause of Death Register will be used to assess the date, place, whether autopsy was performed, and the causes of death throughout follow-up.

### Plans to promote participant retention and complete follow-up {18b}

Trial participation is completely voluntary, and people can withdraw at any time. People who want to withdraw will be asked which trial procedures they want to withdraw from, and whether they consent to be included in the follow-up of the registry-based endpoints. The trial treatment can be changed or discontinued at the discretion of the responsible physician or patient, which is not a reason for withdrawal from the trial. People who change or discontinue their treatment will be included in the analyses in accordance with randomised group (intention-to-treat) and per protocol (actual treatment group).

### Data management {19}

All data will be registered, managed, and stored in a manner that enables correct reporting, interpretation, and verification.

We will use an eCRF which allows for proper audit trial for all entries and changes to data. Descriptions of the methods for data entry and collection, including procedures for verification and validation, will be specified in the study-specific data management plan (DMP). All deviations from the DMP and other information of importance for the study outcome will be reported in the clean file form. Each site keeps a source data location list, identifying where source data are. Data collected from different registers will not be manually entered into the eCRF by site. The principal investigators or authorised designees shall, after verification of data entered by site, lock the data for further editing. By locking, the responsible investigator ensures that all data are correct and complete.

Procedures for data review, database cleaning, and issuing and resolving data queries will be specified in the study specific DMP. After data verification, validation, and all queries are resolved for all people, the database will be closed. All access will be withdrawn except for data export. All handling of all detected errors after database lock will be documented.

The PI and sponsor will maintain the essential clinical investigation documents in the investigation site files archive and sponsor files archive, respectively. The sponsor shall keep all documentation and data for at least 10 years after the trial has ended. The PI will archive all local investigation documentation for at least 10 years or as long as stipulated by the local institution.

### Confidentiality {27}

People who participate in the clinical investigation are coded with a specific clinical investigation identification number. All people are registered in a subject identification list (subject enrolment and identification list) that connects the subject’s name and personal number with a clinical investigation identification number. All data are entered into the eCRF, where access is allowed only with two-step authentication. Paper forms and questionnaires are saved in files that are stored in a locked area. The PI will archive all local investigation documentation for at least 10 years or as long as stipulated by the local institution.

The Swedish Social Security Number and date of randomisation in the trial will be sent securely to the trial unit Blekinge Tekniska Högskola (BTH; Blekinge Institute of Technology) that sends out and administers the patient questionnaires, which will be separate from the trial sponsor and monitor(s). The questionnaires will be posted to the patient at 3 and 12 months (± 2 weeks) after randomisation. All information collected by the sponsor will be pseudonymised and identified with Study ID, with a code list with study IDs and the corresponding Swedish Social Security Numbers safely stored separately.

### Plans for collection, laboratory evaluation, and storage of biological specimens for genetic or molecular analysis in this trial/future use {33}

Non-applicable.

## Statistical methods

### Statistical methods for primary and secondary outcomes {20a}

A detailed statistical analysis plan (SAP) will be established and published in collaboration with a biostatistician before the lock of the database for the primary analysis and before performing each secondary analysis.

The population for efficacy analyses is defined as all randomised people who did not withdraw their consent to be included in the outcome analyses (ITT population). The population for safety analyses is defined as all randomised people who started their randomised treatment (safety population). All analyses will be performed primarily by randomised treatment group (ITT) and secondarily by treatment used (PP).

Data will be summarised using mean with standard deviation and median with range and interquartile range for continuous variables with normal and skewed distributions, respectively. Categorical variables will be expressed as frequencies and percentages. Differences between groups will be analysed using Student’s *t*-tests (for normally distributed continuous outcomes), chi2 tests (for dichotomous outcomes), and Wilcoxon’s rank sum test (for ordinal and non-normally distributed data).

Outcomes will be compared between the treatment groups using multivariable regression models, expressed as point estimates with 95% confidence intervals. The primary outcome will be analysed using Cox proportional-hazards regression. Secondary outcomes will be analysed using appropriate statistical methods: logistic regression for categorical outcomes, Cox regression for standard survival analysis, Fine–Gray regression for competing risk scenarios, and linear regression for continuous outcomes, ensuring robust and context-appropriate analysis. Mixed regression models with random effects will be used to analyse outcomes measured in the same individual at several time points to account for repeated measurements. The outcome analyses will be adjusted for age and sex, the stratification variables, number of hospitalisations during the 12 months before baseline, and time from starting LFOT in Swedevox. Statistical significance will be defined as a two-sided *p*-value < 0.05.

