## Trial design {8}

HILOT is a registry-based, randomized clinical trial (R-RCT) with the aim of investigating whether one of two treatment arms is superior to the other. There are two parallel groups, where the first treatment arm is existing standard treatment with LFOT at least 15 h/day. The second treatment arm also consists of oxygen at least 15 h/day, where LFOT is replaced by HFOT minimum during night-time. During daytime, the patient may choose between HFOT and LFOT.

People with ongoing LFOT are randomised in a 1:1 ratio to standard treatment with LFOT or LFOT with added HFOT during nighttime and at the patient’s discretion daytime (Fig. 1). Randomisation will be performed between the treatment groups using a central, computerised, online procedure, stratified by main reason for the ongoing LFOT (COPD or ILD) and by study centre, in blocks of 2–8 participants. The randomised treatment group will not be blinded for the participants or the study staff for practical reasons but will be blinded for the statistician before the lock of the study database.

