### Methods for additional analyses (e.g. subgroup analyses) {20b}

People with COPD and ILD will be analysed separately. If the projected sample size is not reached, all randomised people can be analysed as a secondary analysis, which will be detailed in the SAP.

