### Methods in analysis to handle protocol non-adherence and any statistical methods to handle missing data {20c}

Missing values of predictors and confounders will be imputed by multiple imputation approaches.

Any trial deviations, including reportion deviations, will be specified in the SAP before each analysis.

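### The SAP for the 3-month and 1-year secondary outcomes may be written after database lock, when the statistician is unblinded and the primary result is known

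*Protocol article*

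**What the plan says.** The section on statistical methods for primary and secondary outcomes {20a} states that a detailed SAP will be established and published "before the lock of the database for the primary analysis and before performing each secondary analysis". The section on non-adherence and missing data {20c} uses the same per-analysis timing for trial deviations, which "will be specified in the SAP before each analysis".

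On blinding, Trial design {8} says that allocation is open to participants and study staff but "will be blinded for the statistician before the lock of the study database". The section Who will be blinded {17a} agrees: "the statistical analyst will remain blinded to allocation until database lock to minimise bias".

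Outcomes {12} lists 23 secondary items, to be evaluated in COPD, in ILD and in all participants. All analyses are to be done first by randomised group and then by treatment used.

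**The concern.** The timing rule has two deadlines, and only one of them is tied to lock. For secondary outcomes the deadline is the start of the analysis itself, which can fall after allocation is revealed and the primary comparison is known.

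This matters because the statistician's blinding is the only masking the article describes. Its stated purpose is to limit bias, and for secondary outcomes the timing rule lets that protection lapse before the plan is fixed. The primary result is also informative about many of the secondaries. Hospitalisation rates, days in hospital and mortality come from the same participants and largely the same events as time to first hospitalisation or death. Someone who knows the primary result can partly foresee which analytic choices would favour either arm.

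**Working it through.** No arithmetic applies. The check is whether the stated rules permit a late plan and, if so, what is still open to choice.

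**Step 1: the order of events that the text permits**

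| Event | Rule in the article | Must it precede lock? |
|---|---|---|
| SAP for the primary analysis | {20a}, first deadline | Yes |
| Database lock; statistician's blinding ends | {8}, {17a} | – |
| Primary analysis | After its SAP | – |
| SAP for a secondary analysis | {20a}, second deadline; {20c} for deviations | No, only before that analysis |
| Secondary analysis | After its SAP | – |

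Followed from top to bottom, this order breaks no stated rule.

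**Step 2: is another reading available?** The sentence in {20a} could mean a single SAP that meets both deadlines. The second deadline would then be redundant, because a plan finished before lock necessarily precedes every later analysis. The wording in {20c} and the staged publications in Dissemination plans {31a} also fit a plan-by-plan reading better. Those publications run from primary and main secondary outcomes to health economics, then additional secondary outcomes including ILD, and later to correlational and long-term work. The late plan is permitted, but not certain.

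**Step 3: what is already fixed.** Outcomes {12} gives the secondary outcomes, their time points and populations, and a definition of time to first exacerbation. Section {20a} gives a regression family by outcome type, the adjustment covariates, and ITT as the leading analysis.

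**Step 4: what stays open until the SAP**

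- *Per-protocol rules.* Every analysis is repeated by treatment used, but the article does not say what amount of HFOT use counts. The Discussion reports that most people randomised to HFOT in the pilot phase stopped it. Procedures were then changed, so that rate may not persist. If use stays low, the per-protocol results will depend heavily on the rule chosen.
- *Models for counts.* The outcomes include hospitalisation rates, days in hospital, ICU admissions and days, and number of exacerbations. The families named in {20a} are logistic, Cox, Fine–Gray, linear and mixed models, so the choice for counts is still to come.
- *Scoring.* Several questionnaires are described as modified, and symptoms and quality of life are measured at 3 and 12 months.
- *Which secondaries are main.* {31a} plans a paper on the primary and main secondary outcomes, but {12} does not rank the list.

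Leaving such details to a SAP is normal and is no fault. The fault is that the SAP settling them may follow unblinding.

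**Step 5: which outputs are exposed.** These are the 3-month and 1-year secondary outcomes in COPD, ILD and all participants, including 1-year health economics. Long-term registry follow-up and correlational work come later by nature, and later plans for them are reasonable.

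**The case against.** The strongest reply is that little freedom remains. Outcomes, populations, model families and covariates are in print, and ITT comes first. The joint paper on primary and main secondary outcomes suggests that the main ones will be planned with the primary. Each SAP is to be published, so a late choice would be visible. Most of this stands, and it limits the size of the problem. It does not remove it: nothing binds the main secondaries to the earlier deadline, and publication reveals the date of a choice without undoing the knowledge behind it.

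A reader might go further in two ways that the article does not support.

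- *Multiplicity.* {20a} says "Statistical significance will be defined as a two-sided *p*-value < 0.05", with no limit to the primary outcome. One might multiply about 20 outcomes by three populations and two analysis sets, reach 120 tests, and expect 120 × 0.05 = 6 false positives. But ranking or adjusting secondary outcomes is commonly left to a SAP, and that SAP is not shown. The count also treats overlapping analyses as separate. The COPD group makes up 270 of the planned 310 participants (87%), the per-protocol analyses reuse the same outcomes, and some listed items are not between-arm tests. With one primary outcome in one population, the primary error rate is not inflated.
- *Pooled analysis.* {20b} says "If the projected sample size is not reached, all randomised people can be analysed as a secondary analysis", whereas {12} evaluates the secondary outcomes in all people without condition. This need not be a contradiction. {20b} can be read as a fallback that pools the primary endpoint, which {12} lists for COPD and for ILD but not for all people.

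**Conclusion.** The point holds as a narrow weakness in timing. The stated rules allow the plan for the 3-month and 1-year secondary outcomes to be fixed after lock, with allocation and the primary result known. The primary outcome, its alpha of 0.05 and the target of 270 with COPD are untouched. The exposure is confined to the choices listed in the fourth step of the working, and the article gives no basis for putting a number on the resulting bias.

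The conclusion assumes that the lock at which blinding ends is the lock for the primary analysis, and that the article's wording reflects the full protocol. If the unseen SAP already covers these outcomes and is signed before lock, practice would be sound and only the wording would need correction. The change is worth making because it is cheap, not because the trial's main conclusion is at risk.

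**What to change.** Amend {20a} so that one SAP is finalised before the first database lock and before the statistician is unblinded. It should cover the primary outcome and all 3-month and 1-year secondary outcomes in COPD, in ILD and in all participants. It should settle the per-protocol rules, the count-outcome models, the scoring, and which secondaries are main. Align {20c}, so that the handling of trial deviations for these outcomes is fixed by the same date. State that later SAPs cover only long-term registry follow-up and correlational work.

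The cost is SAP work brought forward, including the 1-year health-economic and ILD parts. Sample size, alpha and data collection do not change. Recruitment is ongoing and completion is expected in 2028 at the earliest, so there is time.
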